### Podiatric treatment

The participants (n = 100; see Sample size) in the intervention group will be referred to a podiatrist to receive usual podiatric care. The treatment may consist of shoe advice, a silicone toe orthotic or corrective orthotics by means of an insole. Podiatrists are asked to follow the treatment protocol recommended by podiatric department of Fontys University of Applied Sciences. Each participant will be advised to contact the podiatrist if there are any problems with the treatment and an appointment will be made with each participant to examine progress and response to treatment after six to eight weeks. If needed, the treatment will be adjusted. The podiatrist will register details regarding the assessment of the forefoot problem, the diagnosis and treatment decisions on a standardised form.

### Control condition

Participants (n = 100; see Sample size) in the control group will receive a leaflet with shoe advice. The leaflet has been developed in cooperation with the GPs of the Academic Network of the VU University medical centre, the podiatric school of Fontys University of Applied Sciences and 8 podiatrists in the region. Shoe advice is part of the lifestyle advice that is frequently given by GPs to patients with foot problems [13]. Discussions with GPs prior to the trial indicated that this reflects a common minimal and first treatment option; general advice is given to wear well-fitting shoes of good quality and sometimes the patient's shoes are checked and commented on. Some GPs give more specific advice to adapt the shoe or to buy custom made shoe inlays or orthoses. In order to reflect usual care while ensuring optimal contrast between the two treatment groups, we will ask the GPs to refrain from specific individual advice. The participants will be advised to compare their shoes with recommended shoe wear presented in the leaflet and to purchase better fitting shoes if their shoes are not compatible with these recommendations. A reimbursement of € 25,- is given as an encouragement. All patients are invited to contact the research group or their GP for questions regarding the information leaflet. All participating GPs will receive a brief training session on how to provide information based on the leaflet and how to perform a shoe assessment.

### Primary and secondary outcome measures

The primary outcome measures will be forefoot pain intensity scored by the participant on an 11-point pain numerical rating scale (PI-NRS, where 0 = no pain and 10 = worst possible pain), foot function using the 5 point Foot Function Index (FFI-5pt) and foot disability using the FPDI [17,24,25]. The FFI-5pts has been translated into Dutch and validated for similar participants as an interview schedule. The FPDI has been validated for participants with foot problems but was not yet available in Dutch. Within the scope of this trial the FPDI has been translated into Dutch and will be validated according to methods proposed by Beaton et al.[26]. Secondary outcomes include social participation (Keele Assessment of Participation[27]) and Quality of Life (SF-12). Both primary and secondary outcome measures will be collected at baseline and after 3, 6, 9, and 12 months. Data on personal education and work history, shoe history and co-morbidity[28] are collected at baseline as possible effect modifiers or confounders.

### Process evaluation of podiatric treatment

Descriptive statistics will be used to describe the extent to which assessment of the forefoot problem and podiatric treatment decisions concur with the protocol, and if deviations (if any) can be explained.

For each patient in the podiatry treatment group, an expert panel of a podiatrist, a lecturer of the podiatry department of Fontys University for Applied Sciences and a human movement scientist will evaluate whether the diagnoses of the podiatrists are in accordance with the results of their assessment, and whether adequate decisions are made regarding treatment. For this evaluation, the notes of the podiatrists and the results of the entrance examination will be made available to the expert panel.

### Sample size

There are no evidence-based estimates for clinically important change in assessing forefoot pain or for clinically relevant differences between interventions for chronic foot pain. In a previous study it was estimated that a reduction of approximately two points on an 11-point pain intensity numerical rating scale represents a clinically important improvement [29]. We assume that the improvement in the podiatric treatment group will be one point larger than the improvement in the control group (a mean improvement of approximately 2 versus 1 point on the 0-11 point NRS, with an estimated standard deviation of 2.5). In this design the main question is "whether the podiatric treatment is more effective than the control treatment viz. a standardised shoe advice". Therefore we will perform a one-sided statistical test with the null hypothesis that podiatric treatment has either an equal outcome or a worse outcome as compared to standardised shoe advice, both outcomes having an equal clinical consequence [30].

In order to detect a 1 point difference in improvement between the groups after 12 months with a one-sided significance level of 0.05, and assuming a power of 0.8, an ICC between podiatrists and GPs of 0.05, a correlation of 0.50 between repeated measurements and a minimum of 5 patients per care provider, we would need complete data of 75 participants in each study group. We will enrol 2 × 100 patients to allow for a drop-out rate during follow-up of 25%. If every podiatrist will treat a minimum of 5 patients, 15 podiatrists will be needed to deliver the treatment in the entire intervention group.

In 17 practices of the Academic Network, with a total of n = 23,231 patients of 50 years or older, the diagnosis "foot problems" (ICPC 17) or free text words indicating foot problems were noted in the GP records of n = 497 patients within this age group. This incidence (21/1000) is in accordance with a previous estimate of 17/1000 [31]). We expect that about one third of all consulters presenting with foot problems have forefoot problems that meet our criteria [2,5], and assuming about 50% of these patients are eligible and willing to participate, a practice with a population of average age distribution can generate a minimum of 5 participants per year. This means that we will need to recruit at least 40 practices to participate in the trial to achieve the required number of patients.

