### Data analysis

Multilevel analysis will be used to estimate the overall effect of podiatric treatment as compared to standardised shoe advice on the three primary outcome measures (PI-NTR, FFI-5pt and FPDI). Both clustering due to participants being treated by podiatrists and clustering due to repeated measurements within the same individuals will be taken into account. Results will be adjusted for differences in baseline similarity, if these occur. The effect of interest is the treatment × time interaction [32] where the primary focus will be on the primary outcome measures at 3 and 12 months' follow-up. Differences in secondary outcome will be estimated using similar statistical methods. All data will be analysed using an intention-to-treat approach. In all cases, a significance level of 5% is pre-stipulated.

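### The 75 per group fits a linear treatment-by-time slope, but the analysis focuses on separate 3- and 12-month outcomes; an unadjusted 12-month change contrast then has about 72–79% power, not 80%

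*Protocol article*

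**What the plan says.** The Sample size section of the protocol article plans for "a mean improvement of approximately 2 versus 1 point on the 0-11 point NRS, with an estimated standard deviation of 2.5". It tests "with a one-sided significance level of 0.05", "assuming a power of 0.8", "an ICC between podiatrists and GPs of 0.05", a correlation of 0.50 between repeated measurements and at least 5 patients per care provider. The difference is placed at 12 months. The conclusion is that "we would need complete data of 75 participants in each study group", and 100 per group are enrolled to allow for 25% drop-out.

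Under Primary and secondary outcome measures, outcomes are collected at baseline and at 3, 6, 9 and 12 months.

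The Data analysis section plans a multilevel model and states: "The effect of interest is the treatment × time interaction". It puts the primary focus on the primary outcomes at two visits, months 3 and 12. Adjustment for baseline is conditional: it is made if the groups turn out to differ at baseline. The article does not print the sample-size formula.

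**The concern.** The stated target is a difference in improvement from baseline to month 12. Read as a comparison of two change scores, it needs 77.3 per group before any allowance for clustering, which is already above 75. With the stated clustering it needs about 93. So the 75 must come from a model that draws precision from the intermediate visits, and the question is whether the planned analysis uses that model.

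At stake is how a null result at 12 months would be read. If the reported contrast is specific to that visit and unadjusted for baseline, readers would credit the trial with 80% power when it had somewhat less.

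**Working it through.** **Inputs (Sample size section unless noted).** Difference δ = 1; SD 2.5 (variance 6.25); one-sided 0.05 (z = 1.6449); power 0.80 (z = 0.8416); correlation ρ = 0.50; ICC 0.05 with 5 patients per provider, so the design effect is 1 + 4 × 0.05 = 1.20; visits at 0, 3, 6, 9 and 12 months (outcome measures section). The article does not say whether 2.5 is the SD of a score or of a change. At ρ = 0.50 this makes no difference, since 2 × 6.25 × (1 − 0.5) = 6.25.

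For an estimate with per-person variance V, n per group = 2 × (1.6449 + 0.8416)² × V / δ² = 2 × 6.1826 × V, multiplied by the design effect.

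**1. Reproducing the 75.** Take the interaction as a linear slope with equal correlations between visits. The mean visit time is 6 months and the squared deviations sum to 36 + 9 + 0 + 9 + 36 = 90. The variance of 12 × slope is V = 144 × 6.25 × 0.5 / 90 = 5.0.
- n = 2 × 6.1826 × 5.0 = 61.83; × 1.20 = 74.19, so 75.
- Power at 75: SE = √(2 × 5.0 × 1.20 / 75) = 0.400; Φ(2.500 − 1.645) = 80.4%.
- Enrolment: 75 / 0.75 = 100.

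This uses every stated input and returns every stated output. Of the readings tried at the stated one-sided level, it is the only one that gives 75. A two-sided test of the mean of the four follow-ups comes close (73.6, so 74) but contradicts the stated sidedness.

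**2. What that model assumes.** The benefit rises in a straight line to 1 point at month 12, so it is 0.25 point at month 3. If instead the full 1 point were present from month 3 and held, the fitted slope would give 12 × [(−6)(0) + (−3)(1) + (0)(1) + (3)(1) + (6)(1)] / 90 = 0.8 point. Power of the slope test would then be Φ(0.8 / 0.400 − 1.645) = 64%.

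**3. Visit-specific, unadjusted 12-month contrast.** With time as separate visits, complete data and no baseline term, the interaction at month 12 is the difference in mean change from baseline. V = 6.25, and the 3-, 6- and 9-month visits add nothing.

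| Clustering | n needed | SE at 75 | Power at 75 |
|---|---|---|---|
| Design effect 1.20 in both arms | 77.28 × 1.20 = 92.7, so 93 | √(12.5 × 1.20 / 75) = 0.447 | Φ(2.236 − 1.645) = 72.3% |
| Podiatry arm only (average 1.10) | 77.28 × 1.10 = 85.0, so 86 | √(12.5 × 1.10 / 75) = 0.428 | Φ(2.335 − 1.645) = 75.5% |
| None, or a provider effect that cancels from change | 77.28, so 78 | √(12.5 / 75) = 0.408 | Φ(2.449 − 1.645) = 79.0% |

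**4. The same 12-month contrast, always adjusted for baseline.** V = 6.25 × (1 − 0.5²) = 4.6875.
- n = 2 × 6.1826 × 4.6875 = 57.96; × 1.20 = 69.55, so 70.
- Power at 75: SE = √(2 × 4.6875 × 1.20 / 75) = 0.387; Φ(2.582 − 1.645) = 82.6%.
- With clustering in the podiatry arm only, 64 are needed and power at 75 is 85.4%.

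Baseline adjustment also helps the slope. With the arms taken as equal at baseline, V = 3.75, SE = √(2 × 3.75 × 1.20 / 75) = 0.346, and power is Φ(2.887 − 1.645) = 89%.

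**The case against.** A reader might infer that 75 is simply a miscalculation and that the plan's own inputs require 93. The documents do not support that. The inputs include the repeated-measures correlation, the schedule has five visits, and the named effect is the treatment-by-time interaction. Together, on a linear slope, they give 75 and then exactly 100. Under that model, 12 × slope is the 12-month difference in change, so 80% is a coherent claim. The 93 arises only from a two-visit change score with the full design effect in both arms, which is the least favourable reading in the table.

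Nor should the 0.25 point at month 3 be held against the sample size. A 3-month contrast of that size would have about 14% power (Φ(0.25 / 0.447 − 1.645)), but the article claims no power at month 3, and a straight line used for sizing is not a forecast for that visit.

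It is also fair to say that the coding of time and the covariates are commonly left to a full protocol or analysis plan, which is not at hand, and that other readings exceed 80%. The mean of the four follow-ups would need only 58. The missing formula is therefore not the point.

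What remains concerns what the article does fix. A single linear slope cannot estimate the 3- and 12-month effects separately, yet those two visits are the declared focus. Baseline adjustment, which would restore the power, is made conditional on an observed imbalance.

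**Conclusion.** The concern holds as a mismatch between the sizing model and the analysis. The 80% holds for a linear-slope test with a benefit that grows linearly to 1 point at month 12. For the visit-specific, unadjusted 12-month change contrast, power at 75 per group is about 72–79% depending on how clustering enters, a shortfall of roughly 1 to 8 percentage points.

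This rests on complete data, equal correlations of 0.50 between visits, SD 2.5 and one-sided 0.05. The linear-slope origin of the 75 is inferred from its exact match with the inputs. The point deserves correction because the remedy is free, but the size of the shortfall and the unchanged enrolment do not make it critical.

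**What to change.** Keep 2 × 100 and make three wording changes:

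1. In Data analysis, replace the conditional rule with adjustment for baseline PI-NRS in all cases.
2. Name the baseline-adjusted 12-month contrast from the multilevel model as the one for which the trial is sized.
3. In Sample size, restate the calculation: with design effect 1.20, about 70 completers per group are needed, and 75 give about 83% power at one-sided 0.05.

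If the slope is kept as the target, state that the 80% assumes linear growth of the benefit over 12 months. If the unadjusted change contrast is kept, restate its power as about 72% (design effect 1.20 in both arms).

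The cost is rewording of two sections. Baseline PI-NRS is already collected, so no extra patients, visits or measurements are needed.

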### Treatment allocation and adherence

After providing informed consent, randomisation will be performed based on an allocation schedule that is generated before the start of the trial by a computerised random number generator using block randomisation with blocks of 8 or 4 with pre-stratification for gender and age (<75, ≥ 75). Since the age group ≥ 75 is expected to be smaller, a block of 4 has been chosen to increase the likelihood of equal distribution over the control and intervention groups. An independent research assistant will prepare coded sealed envelopes containing the treatment allocation. After baseline measurements the correct allocation envelope is opened by the participant. The foot examiner will be blinded for the random sequence and will not be informed of the block size ensuring concealed allocation of treatment. All GPs will be notified about the participants' allocated treatment, and will be asked to stimulate adherence to treatment whenever the participant contacts the GP during the intervention period. If symptoms do not improve despite adherence to treatment during the 3 months following randomisation, or with deterioration of the foot problem, the GP is free to provide another treatment or refer the participant for further treatment elsewhere.

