### Inclusion procedure

Potential participants will be recruited by three different methods. First, in all participating practices a retrospective search of the medical records will be carried out to identify all people aged 50 and over who have consulted their GP for a forefoot problem in the year preceding the start of the study. Second, all older people who consult their GP for forefoot problems during a period of 12 months following the start of the study will be considered for participation (prospective recruitment). Finally, all people visiting the general practice (for any reason) will be informed about the study by putting up posters in the waiting area of the GP clinics inviting patients to contact their GP if they have forefoot pain.

All potentially eligible patients will be invited to participate in the study and will receive comprehensive information about the study, a screening questionnaire and a pre-paid envelope to return the consent form and the questionnaire. Non-responders will receive a reminder after 2 weeks.

In addition to the assessment by the GP, inclusion and exclusion criteria will be assessed using self-report information from the screening questionnaire. Forefoot pain intensity is scored using a 0-10 point numerical rating scale and the location of pain is indicated on a foot manikin [17]. The area that will lead to inclusion in the study is shown in figure 2. Foot disability is assessed by the Foot Pain and Disability Index (FPDI) [17,18].

All patients who are potentially eligible for the study based on the screening questionnaire will be invited for a foot examination details of which will be discussed below (see Foot examination). The purpose of the foot examination is to measure baseline foot and pressure characteristics and to assess eligibility to participate in the trial. If the foot problem of the patient is considered to be too severe, and neither podiatric treatment nor shoe advice is considered adequate treatment, or if there are signs of any of the exclusion criteria like diabetic neuropathy, the patient will be referred back to their GP. If patients meet all eligibility criteria, written consent to participation in the trial will be obtained and a unique study number will be allocated to the participant.

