### Foot examination

A foot examination will be performed at baseline before randomisation to assess eligibility. Additionally, 25 participants from the podiatry group will be asked to attend a second foot examination after three months to enable the process evaluation (see process evaluation of podiatric treatment). The presence of diabetic neuropathy in the forefoot will be ruled out based on tests using a 10 gram Weinstein monofilament and a 64 Hz tuning-fork. With the participant having his or her eyes closed, the skin on the plantar skin of the hallux and the MTP joints of I and V will be touched with the monofilament, and two out of three touches must be perceived. The vibrating tuning-fork is placed on the medial side of MTP1 and on the lateral side of MTP5; the vibration must be perceived for more than 5 seconds. Digital photographs of the ventral, lateral and medial side of the foot and shoes will be taken on a surface containing measurement lines in centimetres. Participants will be asked to bring the shoes they wear most often for this assessment and for the pressure measurements. Next, the Foot Posture Index will be assessed and scored according to Redmond et al.[19]. To assess pressure distribution patterns during barefoot and shod gait Emed-X (Novel gmbh, Münich, Germany) [20] and Pedar-X (Novel gmbh, Münich, Germany) [21,22] will be used. The Emed platform (4 sensors per cm2, sample frequency 100 Hz) is imbedded in a polyethylene walkway. A two-step protocol will be used for the barefoot pressure measurements, and each foot will be measured 3 times [23]. Each participant will be asked to walk at their preferred speed and with their preferred step length, in other words "as normally as possible". Everyone will have at least two practice runs per foot before the actual measurements are made. Participants are asked to look straight ahead to prevent targeting; if targeting is suspected, the measurement will be discarded and a new run will be executed. For the in-shoe pressure measurements an adequate size sensor-insole will be placed in the shoe (99 sensors/insole, 100 Hz). Participants will be asked to walk back and forth until twelve steps per foot are obtained. First steps, final steps and steps while turning will be excluded from the measurements.

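### One fixed block size per age stratum in an open trial: not telling the foot examiner the size does not by itself ensure concealed allocation

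*Protocol article*

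**What the plan says.** The section on treatment allocation and adherence describes a computer-generated schedule, prepared before the trial starts, "block randomisation with blocks of 8 or 4 with pre-stratification for gender and age (<75, ≥ 75"). It ties the smaller block to the older group: "Since the age group ≥ 75 is expected to be smaller, a block of 4 has been chosen", the reason given being balance between the arms. The block of 8 for the under-75s is not stated outright but follows. Nothing says that sizes vary within a stratum, and stratification by practice is not mentioned.

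An independent research assistant prepares coded, sealed envelopes, and the participant opens the envelope after the baseline measurements. On concealment the section says: "The foot examiner will be blinded for the random sequence and will not be informed of the block size ensuring concealed allocation of treatment". GPs are told the allocation of their participants.

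The trial design section calls the trial open. The foot examination takes place before randomisation and serves to assess eligibility. One ground for sending a patient back to the GP at that point, in the inclusion procedure section, is a judgement: "If the foot problem of the patient is considered to be too severe, and neither podiatric treatment nor shoe advice is considered adequate treatment". The participants section gives the severity judgement to the GP or the study team.

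**The concern.** Concealment can fail in two ways: someone reads the next allocation, or someone predicts it from earlier ones. Sealed envelopes from an independent assistant deal with the first. The second depends on the block structure and on who knows past allocations.

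With one constant size in a stratum, the end of every block is determined once one arm has been used up. Withholding the size makes this harder but does not prevent it. A constant size can be worked out from a run of known allocations, and here both sizes and the age rule are printed in the article. Because the trial is open, past allocations are not masked by design.

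At stake is selection bias. If the next allocation could be foreseen where a patient may still be judged too severe, the decision to enrol could depend on the arm. The primary and secondary outcomes are self-reported by participants who know their treatment, so masked outcome assessment could not offset such a bias.

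**Working it through.** The article gives no figure for predictability, so there is none to reproduce.

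**Inputs**
- Block size *B*: 4 for age 75 or over (stated) and 8 for under 75 (implied), both from the treatment allocation section.
- Allocation 1:1, from the sample size section: "We will enrol 2 × 100 patients to allow for a drop-out rate during follow-up of 25"%.
- Share of participants aged 75 or over: not given. Assumed to be 10%, 20% or 30%.
- Observer: knows *B* and holds a complete tally by gender and age. This is an assumption and the worst case.

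**Allocations that are certain.** An allocation is forced once one arm has used its *B*/2 places. The expected number per block is *B*/(*B*/2 + 1), so the share is 1/(*B*/2 + 1).
- *B* = 4: 4/3 = 1.33 per block, or 33.3%. By listing: of the 6 possible blocks, AABB and BBAA each have 2 forced allocations and the other four have 1 each, so 8/6 = 1.33.
- *B* = 8: 8/5 = 1.60 per block, or 20.0%. Enumeration of all 70 blocks agrees.

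**Best guess over all allocations** (always guess the arm that is behind, 50:50 when level).
- *B* = 4: by position, 0.5, 2/3, 2/3 and 1. The sum is 2.833, and 2.833/4 = 70.8%.
- *B* = 8: 66.6% by enumeration.

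This rule needs only the tally, not the block size.

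**Overall certain share** = *s* × 1/3 + (1 − *s*) × 1/5, where *s* is the share aged 75 or over.

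| *s* | Share | Of 200, complete blocks | Of 200, unfinished last blocks allowed for |
|---|---|---|---|
| 10% | 21.3% | 42.7 | about 41 |
| 20% | 22.7% | 45.3 | about 43 |
| 30% | 24.0% | 48.0 | about 46 |

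The last column is a simulation that also assumes 70% women.

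**How far each route reveals past allocations**
- *GPs.* The sample size section plans at least 40 practices, and 200/40 = 5 participants each. A GP sees about 5 of 200 allocations (2.5%), scattered over four trial-wide lists.
- *Second examination.* The foot examination section says "25 participants from the podiatry group will be asked to attend a second foot examination after three months". That is at most 25 of 200 (12.5%), all from one arm and three months late. With even recruitment over 12 months, 200 × 3/12 = 50 people enter in between. If 20% are 75 or over and 70% are women, those 50 fill 28/8 = 3.5 and 12/8 = 1.5 blocks in the younger strata, and 7/4 = 1.75 and 3/4 = 0.75 in the older. Most blocks would have closed.
- *Opening of the envelope.* This is the only route that could supply a full tally. The article does not say whether the examiner is present or is told.

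**Effect of varying the sizes.** Simulation, sizes drawn with equal probability, observer knowing the menu of sizes and the full history:
- 4, 6 and 8: about 2% certain, best guess about 67% to 68%.
- 4 and 6: about 6% certain, best guess about 68% to 69%.

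At *s* = 20% the certain share becomes 0.2 × 6% + 0.8 × 2% = 2.8%, about 6 of 200 instead of about 45.

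**The case against.** The safeguards are real: a computer-generated list, an independent preparer, coded sealed envelopes, a withheld block size, and opening only after consent and baseline measurements. Eligibility is already settled before the envelope is opened. Certainty would need both the block size and a running tally in four strata, and no passage says that the examiner has either. The severity judgement is not given to the examiner alone, and its wording, that neither treatment is adequate, favours neither arm. The block of 4 was chosen for a stated reason, balance in a small group.

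All of this stands, and it limits the point. A reader might infer that concealment has failed, or that a fifth to a third of allocations will be known in advance. The documents do not support that. The shares are conditional on knowledge that is not shown to exist, and the third applies only to the older group, which is expected to be smaller. A reader might also infer that GP notification or the repeat examination gives allocations away, but both reveal too little. Nor do the documents show whether the article, with its printed sizes, appeared while recruitment was open.

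What the objection does not rescue is the assurance itself. Not telling one person the size of a constant block makes prediction harder; it does not ensure concealment.

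**Conclusion.** The point holds in a limited form. A constant block size within each age stratum, in an open trial with a judgement on severity before randomisation, cannot ensure concealment merely because the examiner is not told the size. The worst case is 33% of allocations foreseeable in the strata aged 75 or over and 20% in the younger strata, or about 21% to 24% overall if 10% to 30% of participants are 75 or over. This rests on an observer with the block size and a complete tally by stratum, on the inferred block of 8, and on the assumed age share. It shows a weakness that is easily removed, not evidence that bias will occur.

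**What to change.** Generate the schedule with block sizes varied at random within each gender-by-age stratum. Keep the sizes small in the older strata (for example 4 and 6), to respect the stated balance reason, and use for example 4, 6 and 8 in the younger strata. Do not disclose the sizes until recruitment ends. If recruitment has begun, apply this to the unused part of each list. If the schedule is kept as it is, drop the assurance and state who learns each allocation and when.

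The cost is a new list and new envelopes from the same independent assistant. The largest possible imbalance within a block is half its size, so it rises from 2 to 3 in each older stratum and stays at 4 in each younger one. The limit of the change should be stated: an observer with a full tally could still guess right well over half the time, so the gain is mainly fewer certain allocations.
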